### Outcomes

The primary outcome is the assessment of perceived dyspnea in all sessions in both groups using the modified Borg scale [14].

The secondary outcome is the assessment of patient experience at the end of the early mobilization protocol with and without immersive VR using the Net Promoter Score (NPS) tool and the Likert scale [15] as well as an open-ended interview.

Other variables include (a) assessment of vital signs, (b) collection of sociodemographic data, (c) assessment of risk of falls, and (d) assessment of functional independence. To assess the risk of falls, the standard Severo-Almeida-Kuchenbecker (SAK) 2 scale [16] will be used. To assess functional independence prior to hospitalization, the Barthel scale [17] will be used. Both scales are validated.

### Participant timeline and study protocol

The study protocol is shown in Fig. 2. The informed consent will be obtained by one of the researchers. The study begins with the daily screening of hospitalized patients with HF, performed 7 days per week, in the morning and afternoon shifts, using the electronic access to patients admitted to the ICU. Baseline measurements will be performed before randomization, when the patient has potential eligibility to be included, is cleared to start early mobilization, and has accepted.

Patients with potential eligibility, but who for any clinical reason were unable or refused to participate in the study, will be included in a screening exclusion worksheet with coded patient identification data, the date, and the reason for non-inclusion to later report this information.

The team responsible for conducting the intervention and collecting variables will receive training from the research team prior to collection, and patients will be monitored daily by the research team while in the study protocol. The study period will be 1 to 3 days, during this phase, patients will be subjected exclusively to the mobilization protocol proposed by the study. Therefore, the patient should not do early mobilization exercises with the hospital physical therapy team.

However, patients in both groups are allowed to do breathing exercises, get out of bed, and walk to perform daily activities (such as bathing, sitting in a chair, etc.) with the multidisciplinary team (nursing or physical therapy), since the sessions with the research team last about 40 min and the patient would not benefit from staying in bed for 24 h. After the study period, the health care team will continue to treat patients according to standard practice or hospital protocol.

After randomization, the first patient contact will include an assessment of perceived dyspnea according to the modified Borg scale [14] and vital signs at rest and immediately after the assessment. In the first day, patients will perform 10 min of in-bed cycle ergometry (5 min for upper limbs and 5 min for lower limbs). After a 24- to 30-h break, perceived dyspnea and vital signs will be reassessed, and the patient will perform training in orthostatic position in addition to in-bed cycle ergometry. On the last day of intervention, 24 to 30 h after the previous intervention, variables will be reassessed again pre- and post-intervention and the patient will walk for 5 to 10 min.

Cardiovascular rehabilitation in the hospital phase aims to optimize both physical and psychological outcomes for the patient. The goal at this juncture is not necessarily intensive rehabilitation, but to initiate a process that ensures patient safety and comfort while also laying the groundwork for post-discharge activities. At this stage, mild-intensity exercises are deemed optimal [18], and the proposed timings sufficiently meet this intensity. Monitoring of vital signs and of the patient’s perception of exertion is essential to maintaining this balance.

All interventions will be performed with or without the use of immersive VR headsets, videos, and earbuds, as previously described. To assess patient opinion at the end of interventions, the NPS tool and the Likert scale [15] will be used. In addition, an open-ended interview will be conducted to further explore quantitative results related to patient experience regarding the proposed interventions in both groups.

Regarding adherence to the study protocol, the research team highlights that mobilization therapy is recommended in the usual treatment of hospitalized patients with ADHF. The proposed exercise protocol does not differ from the mobilization therapy currently offered by the hospital care team; the only difference is the impact evaluation of using VR during mobilization. If patients accept to participate, the research team will explain to both groups that the study requires some additional tests before starting the mobilization protocol, immediately after, and up to 2 days at the end of the protocol. The research team is responsible for reinforcing the importance of the mobilization protocol and the test to participate in the study.

### Sample size

The study by Nomura et al. [19] used the Borg scale in the first 24 h to assess the effects of medication on the sensation of dyspnea and other outcomes. In the first 24 h, the patient’s sensation of dyspnea significantly improved, with a significant reduction in the Borg scale score [19].

Initially, applying the Borg scale obtained an index of 7. After intervention, the index ranged from 2 to 3. This study showed that after the first 24 h the patient tends to have less changes in the dyspnea sensation, given the use of medication [19]. Based on the literature, we believe that 1 point is a considerable change score, since the patient would probably not have a more significant change due to the compensation of the clinical condition.

The sample size was estimated to detect differences in mean dyspnea between the intervention and control groups using the Borg scale, with a difference of 1 point being relevant for the study. For this purpose, the online version of the power and sample size (PSS) Health tool was used [20]. Considering an 80% power, a 5% significance level, and a 1.6-point standard deviation [19, 21], a total sample size of 54 participants was calculated, with 27 participants in each group. To account for 20% of possible losses and refusals, the total sample size will need to include 66 participants (33 in each group). Seeking to reach the appropriate sample number to conclude the study, a daily screening will be carried out by the research team of patients meeting the inclusion criteria admitted to the study site.

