### Randomization and allocation sequence

The Research Electronic Data Capture® (REDCap®) software will be used for randomization. After agreeing to participate in the study, patients will sign an informed consent form. The research team will add in REDCap® the following information: sociodemographic data (age, schooling level, profession, religion, etc.) and clinical data (disease profile, New York Heart Association [NYHA] classification, previous hospitalizations in the last 12 months, other diseases, HF etiology, application of the Borg, SAK 2, and Barthel scales). After all variables are included, the electronic platform randomizes the patient. The allocation sequence is a randomization based on a single 1:1 sequence.

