### Statistical analysis

The database will be built on the REDCap® platform. All data will be analyzed on Statistical Package for the Social Science (SPSS) version 22.0 for Windows®. The Shapiro–Wilk test will be used to assess data normality. For quantitative data, categorical variables will be expressed as absolute and relative frequencies, and continuous variables will be expressed as means and standard deviations or medians and interquartile ranges.

To address the statistical analysis of multiple time point measurements for the primary outcome intragroup and intergroup, repeated measures tests will be done using Generalized Estimating Equations (GEE). Also, associations between vital signs and perception of dyspnea will be analyzed by the GEE test too.

Chi-square will be used for association of categorical variables, and analysis of variance (ANOVA) or Kruskal–Wallis to compare the categorized sensation of dyspnea with the other variables. Depending on variable behavior or characteristic, the correlations will be analyzed by the Pearson or Spearman coefficient. The significance level will be set at 5% (*p* < 0.05). All analyses will be performed by intention to treat.

Information obtained from the Likert scale and the NPS tool will be analyzed using resources from the NVivo software version 12 for Windows®, which combines the main tools required for working with texts, mixed methods, and data from the literature.

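### The sample size of 27 per group does not follow from the inputs stated for it, which need 41 to 42 per group

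*Protocol article*

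**What the plan says.** The Sample size section of the protocol article names the comparison: "The sample size was estimated to detect differences in mean dyspnea between the intervention and control groups using the Borg scale". The target is a 1-point difference. The section then gives the remaining inputs and the result: "Considering an 80% power, a 5% significance level, and a 1.6-point standard deviation [19, 21], a total sample size of 54 participants was calculated", split equally into 27 per group. The allowance for losses follows: "To account for 20% of possible losses and refusals, the total sample size will need to include 66 participants (33 in each group"). Under Randomization and allocation sequence, allocation is 1:1: "The allocation sequence is a randomization based on a single 1:1 sequence".

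The section does not say whether the test is one- or two-sided. It gives no number of measurements per patient, no within-patient correlation and no baseline adjustment. Elsewhere, the Outcomes and Data collection sections have dyspnea scored before and after every session. Intervention and groups allows at most three sessions, and Statistical analysis plans GEE for the repeated measurements.

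**The concern.** The section describes an ordinary comparison of two independent means and gives a difference, an SD, a power and a significance level. A reader with those four numbers can repeat the calculation, and the answer is about half as large again as the stated one. That gap is too wide for rounding or for differences between programs.

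This is the only justification given for the size of a superiority trial on its primary outcome. If the 80% is taken at face value, a non-significant result may be read as stronger evidence against a 1-point benefit than the stated inputs support. Someone sizing a later trial from this protocol would carry the same figure forward.

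**Working it through.** **Inputs.** All are from the Sample size section, except the allocation ratio (Randomization and allocation sequence) and the sidedness, which is assumed.

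- Difference: 1 point
- SD: "a 1.6-point standard deviation"
- Power 80% (z = 0.842)
- Significance level 5%; two-sided assumed (z = 1.960), one-sided also tried (z = 1.645)
- Allocation 1:1

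**Attempt to reproduce 27 per group**

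Normal formula: n per group = 2 × (z for alpha + z for power)² × SD² / difference².

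- Two-sided: 2 × (1.960 + 0.842)² × 1.6² / 1² = 40.2, so 41 per group (82 in total).
- Two-sided t-test (noncentral t): 41.2, so 42 per group (84 in total).
- One-sided 5%: 31.7, so 32 per group; by t-test 32.4, so 33.
- Wilcoxon test instead of the t-test: the two-sided requirement rises to 43 to 44 per group.
- Paired or one-sample t-test with SD 1.6: 22.1, so 23. This is not the comparison described.

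None of these gives 27 per group or 54 in total.

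**Power on the stated inputs** (single time point, unadjusted t-test, difference 1, SD 1.6)

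| Analysed per group | Two-sided 5% | One-sided 5% |
|---|---|---|
| 27 | 61.6% | 73.3% |
| 33 (all 66 analysed) | 70.6% | 80.7% |
| 42 | 80.8% | 88.4% |

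With 27 per group, two-sided, the difference detectable with 80% power is 1.24 points (1.22 by the normal formula: 2.802 × 1.6 × √(2/27)).

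**What would give about 27 per group.** Each route needs an input that the section does not state:

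- an SD of about 1.29 instead of 1.6;
- a difference of about 1.22 to 1.24 points instead of 1;
- adjustment for a baseline score correlated about 0.58 with the outcome: 40.2 × (1 − 0.58²) = 26.7;
- the mean of three sessions with between-session correlation 0.5: 40.2 × (1 + 2 × 0.5)/3 = 26.8.

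**Sensitivity of the last route.** For the mean of three sessions, the variance is multiplied by (1 + 2ρ)/3. Two-sided t-test power at 27 per group for 1 point, with ρ assumed:

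| ρ | Variance factor | Power |
|---|---|---|
| 0.3 | 0.533 | 87% |
| 0.5 | 0.667 | 79% |
| 0.7 | 0.800 | 71% |
| 0.8 | 0.867 | 68% |

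**Loss allowance.** 27 × 1.2 = 32.4, so 33 per group, which reproduces 66. Allowing for 20% lost means dividing: 54/0.8 = 67.5, so 68. With 66 enrolled, 54/66 = 0.818, so 54 remain after about 18% loss.

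**The case against.** The strongest reply is that the trial will not be analysed by a single-time-point t-test. Dyspnea is recorded around each session and analysed by GEE, so the 62% belongs to an analysis that the protocol does not plan. Averaging three sessions with correlation 0.5 gives 26.8, which rounds up to exactly 27, and baseline adjustment with a correlation near 0.6 does about as well. An unreported calculation of this kind may lie behind the figure, and a condensed article may have left it out.

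This stands as a limit on the conclusion. A reader might infer that the trial itself has only 62% power and would miss a true 1-point effect about four times in ten. The documents do not support that, because the power of the GEE depends on correlations and on a choice of contrast that they do not give. Nor does the section list every input: sidedness, the number of measurements and the correlation are absent, and it does not say whether the SD is for raw or change scores.

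The reply does not rescue the stated figure. The section describes a plain difference in group means and attributes 54 to the inputs it names, and 54 does not follow from them. If a correlation was used, it is an essential input that is not reported. The three-session explanation also needs three sessions per patient, whereas the protocol sets three as a maximum and gives a study period of 1 to 3 days.

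On losses, adding 20% is a common convention and the gap is two patients. It is a matter of wording only.

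**Conclusion.** The point holds as a mismatch between the stated inputs and the stated result. A 1-point difference with SD 1.6, 80% power and two-sided 5% needs 41 to 42 per group, against 27 stated. A one-sided test does not close the gap. For a single-time-point comparison on those inputs, 27 per group give about 62% power two-sided (73% one-sided), and analysing all 66 gives about 71% two-sided.

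These percentages assume an unadjusted two-sample t-test. The power of the planned GEE may be higher and cannot be determined. Under the assumed correlations of 0.3 to 0.8, the mean of three sessions gives about 87% down to 68%, a range that includes 80% but does not guarantee it. For the same reason, it cannot be claimed that combining sessions or adjusting for baseline restores 80% power: that too depends on correlations the article does not give. Nor does it follow that 84 patients must be enrolled.

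**What to change.** Correct the Sample size section in one of two ways, without enrolling more patients.

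1. If the calculation was a simple two-group comparison, restate the power to match the inputs: with 27 analysed per group, SD 1.6 and two-sided 5%, about 62% for 1 point, or 80% for about 1.24 points. Say that this is for a single time point.
2. If a repeated-measures or baseline-adjusted calculation was used, state the sessions combined, the correlation assumed, the sidedness and the resulting power. Name the GEE contrast it refers to as the primary analysis, so that the sizing and the analysis match.

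In either case, describe the loss allowance as about 18%.

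The cost is a revised paragraph and, under the first option, a less favourable stated power. Nothing changes for patients or in the conduct of the trial.

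### The planned 27 per group does not follow from the printed inputs (1 point, SD 1.6, 5%, 80% power), which require about 42 per group for a two-sided comparison of means

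*Protocol article*

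**What the plan says.** The protocol article's Sample size section describes the target as a comparison of two group means: "The sample size was estimated to detect differences in mean dyspnea between the intervention and control groups using the Borg scale". One Borg point is the effect it treats as worth detecting. It then gives the remaining inputs and the result: "Considering an 80% power, a 5% significance level, and a 1.6-point standard deviation [19, 21], a total sample size of 54 participants was calculated", split as 27 per group. An allowance of 20% for losses and refusals raises this to 66 (33 per group). The calculation is attributed to a named online sample size tool, whose settings are not shown.

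Allocation is equal: "The allocation sequence is a randomization based on a single 1:1 sequence" (Randomization and allocation sequence). Neither the Sample size section nor the Statistical analysis section says whether the 5% level is one-sided or two-sided.

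The Outcomes section defines the primary outcome as dyspnea in all sessions, the Data collection section has it read before and after each session, and the Statistical analysis section plans GEE for these repeated measurements. The Sample size section mentions no repeated readings, within-patient correlation or baseline adjustment.

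**The concern.** Apart from sidedness, the section prints everything needed to fix the size of a two-group comparison of means, so a reader can check the result, and it does not come out. The gap is 15 per group, too large for rounding or for differences between software packages.

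The 80% power for 1 point is the only justification given for the size of this superiority trial. If it is taken at face value, a non-significant result may be read as good evidence against a 1-point benefit. On the printed inputs the design does not support that reading.

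**Working it through.** **Inputs.** Difference 1 point, SD 1.6, power 80% and significance 5% (Sample size); allocation 1:1 (Randomization and allocation sequence). Standardised difference d = 1/1.6 = 0.625. Two-sided testing is assumed as the usual reading, with one-sided shown beside it.

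**Attempt to reproduce 27 per group.**

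- Normal approximation, two-sided: n = 2 × (1.960 + 0.842)² × 1.6² / 1² = 40.2, so 41 per group.
- Two-sample t-test (noncentral t), two-sided: n = 41.17, so 42 per group, 84 in total.
- Two-sample t-test, one-sided 5%: n = 32.35, so 33 per group.

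None gives 27. Against 84, the stated 54 is short by 30/84 = 36%.

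**Power for 1 point at SD 1.6, single reading, t-test.**

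| Evaluable per group | Two-sided 5% | One-sided 5% |
|---|---|---|
| 26.4 (33 less 20%) | 60.6% | 72.4% |
| 27 | 61.6% | 73.3% |
| 33 (no losses) | 70.6% | 80.7% |
| 42 | 80.8% | 88.4% |

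**What 27 per group does provide.** For 80% power two-sided the detectable d is 0.777. That is 0.777 × 1.6 = 1.24 points, or 1 point if the SD were 1/0.777 = 1.29.

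**Could the repeated readings account for 27?** The article gives no correlation, so the values below are assumptions. For the mean of m equally correlated readings, the SD becomes 1.6 × √((1 + (m − 1)ρ)/m). Two-sided power at 27 per group for 1 point is then:

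| Correlation ρ | Three readings each | Two readings each |
|---|---|---|
| 0.3 | 87% | 80% |
| 0.4 | 83% | 77% |
| 0.5 | 79% | 74% |
| 0.6 | 75% | 71% |
| 0.7 | 71% | 69% |
| 0.8 | 68% | 66% |

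With three readings, 27 per group gives 80% at ρ of about 0.47. Adjustment for a baseline correlated r with the outcome multiplies the SD by √(1 − r²); at r = 0.6 the SD is 1.28 and n = 26.7, so 27. Either route reaches 27, but each needs an input that the section does not print.

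**The case against.** The strongest reply is that the comparison checked here is not the planned analysis. The primary outcome is read in every session and analysed by GEE, and a Borg score is taken before randomization. An analysis that uses several readings, or a baseline, can need fewer patients than a single-reading t-test. The article condenses a fuller protocol and the tool's settings are not visible, so an unprinted input is as plausible as an arithmetic slip.

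Much of this stands. A reader might infer that the trial has 62% power, or that it would miss a true 1-point benefit nearly 4 times in 10. The documents do not support either as an unconditional statement. Both figures belong to one reading, a two-sided test, no baseline adjustment and 27 evaluable per group. With all 33 per group evaluable, the single-reading figure is already 70.6%, and the GEE could lie well above or below 80% depending on the correlation.

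What does not stand is that this rescues the printed figure. The section attributes 54 to the listed inputs and does not link the calculation to the GEE. Nor are three readings per patient assured: the Intervention and groups section sets three sessions as a maximum, and the timeline section gives a study period of 1 to 3 days. One-sided testing does not help either. It needs 33 evaluable per group, whereas the plan's 33 already contains the allowance for losses, and no one-sided test is stated.

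**Conclusion.** The point holds as a mismatch between printed inputs and printed result. A difference of 1, SD 1.6, 5% significance and 80% power require 42 per group two-sided or 33 one-sided, not 27. On those inputs a single-reading two-sided comparison has about 62% power at 27 evaluable per group, about 61% after the planned 20% loss from 33, and about 71% if nobody is lost; 80% power is reached only for about 1.24 points.

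This rests on the two-group comparison of means that the section itself describes. The power of the planned GEE may be higher, but it cannot be determined from the article. The documents also do not show whether the cause is a wrong number or an omitted input. Either way the sentence needs correcting, because it states the trial's main design property and is not true as written.

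**What to change.** Correct the Sample size section, without enrolling more patients, in whichever of two ways matches what was done.

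(a) If no further input was used, keep 54 evaluable and restate the property: about 62% power for a 1-point difference at SD 1.6 (two-sided 5%), or 80% power for about 1.24 points.

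(b) If another SD, a repeated-measures formula or a baseline adjustment was actually used, print that input (the SD, or the number of readings and assumed correlation). State the power for the GEE contrast it refers to, allowing for patients with fewer than three sessions. The input should be the one used in the calculation. A correlation or a summary of sessions picked afterwards because it yields 27 would redefine the primary contrast to fit the number.

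In both cases state the sidedness, and say that a null result will be interpreted by its confidence interval against the 1-point difference.

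Cost: a corrected sentence or two, with no new patients or data. The stated power may become less favourable, or an extra assumption is disclosed.

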### Recruitment

Potential eligible participants will be recruited by an active daily electronic search of patients admitted to the ICU. The research team will be available in the morning and afternoon shifts. All potentially eligible participants will be screened and, if they meet the inclusion criteria, will be approached in the inpatient unit.

